### Land-based exercise programme

Prior to the first land-based exercise session, participants will be tested in a one-repetition maximum test (1-MR) of knee extensors and flexors [41]. This 1-MR will be performed again after 4 weeks of the intervention.

The training programme of land-based resistance exercises will be conducted as follows.

In weeks 1 and 2, exercises will be performed in the supine (hip flexion), lateral (adduction and abduction), prone (hip extension and knee flexion), sitting (knee extension) and upright positions (mini-squat): knee exercises with two sets of 12 repetitions at 50% of 1-MR; hip exercises with two sets of 10 repetitions at 1 kg load; and mini-squats in two sets of 10 repetitions. Both concentric and eccentric movements will be performed at a slow speed.

In weeks 3 and 4, the same positioning will be used for exercises, increasing knee loads to 75% of 1-MR and hip loads to 2 kg. The same number of sets and repetitions will be performed, at low speeds.

In weeks 5 and 6, exercises will be performed in the supine (adduction), prone (abduction and knee flexion), upright (hip flexion and extension) and sitting positions (knee extension). After a new 1-MR testing, loading will be changed to 40% of 1-MR for knees and remaining at 2 kg for hips. Participants will maintain the same number of sets and repetitions, performing concentric movements at a high speed. For mini-squats, one set will be performed at high speed.

In weeks 7 and 8, the same positioning and number of sets and repetitions will be maintained, but increasing the loads to 60% of 1-MR for knees and 3 kg for hips. Concentric and eccentric movements will be performed at higher speeds.

In weeks 9 and 10, positioning and loading will be maintained, with the addition of one set for each exercise, performed at high speeds.

### Aquatic exercise programme

Aquatic training will be conducted in a hydrotherapy pool of 12 m^2^ with access ramps and handrails. Water temperature will be maintained at 32°C. Prior to the first exercise session, volunteers will participate in one training session for familiarisation with the aquatic environment.

Exercises will be performed in an upright position, with water up to the xiphoid process of the volunteers. Open-chain exercises will include hip and knee flexion and extension, adduction and abduction. Closed-chain exercises will include a movement of combined hip and knee extension over a flotation accessory. Overloading in the aquatic programme will be achieved by increasing the velocity and duration of movements and adding flotation accessories.

The training programme of aquatic resistance exercises will be conducted as follows.

In weeks 1 and 2, two sets of 30 seconds of each exercise will be performed without flotation accessories for open-chain movements. Only concentric movements will be performed at a high speed.

In weeks 3 and 4,the same sets and movements will be performed with flotation accessories on lower-limb extremities for increased loading.

In weeks 5 and 6, two sets of 60 seconds of each exercise will be performed, with concentric and eccentric movements at high speeds, without accessories for open-chair exercises.

In weeks 7 and 8, two sets of 60 seconds of exercises will be performed with flotation accessories on lower-limb extremities. Concentric and eccentric movements will be performed at higher speeds.

In weeks 9 and 10, three sets of 60 seconds of exercises will be performed with flotation accessories and both concentric and eccentric movements at higher speeds.

### Control group

Volunteers randomised to the control group will be instructed not to participate in physical activities that include strengthening exercises for the legs. During the 10 weeks of interventions, they will receive telephone calls once a week. In these telephone calls, a trained researcher will interrogate them about events of health problems, temporary disabilities or pain in the lower limbs, recording any clinical complications or medication use. The researcher will reinforce their obligation to maintain normal daily activities and avoid strengthening exercises. After this period, these volunteers will have the choice to participate in one of the two types of interventions in the same programme as the other groups.

### Statistical analysis

For data analysis, we will use the Statistical Package for the Social Sciences version 15.0 (SPSS Inc., Chicago, DE, USA). The baseline characteristics of the sample will be described in frequencies or measures of central tendency and dispersion. The effects of exercise programmes will be evaluated by intention-to treat analysis. The number needed to treat for the study outcomes will be calculated considering values of minimum clinically important difference as positive effects. Repeated-measures analysis of variance for mixed design and two factors will be conducted with preplanned contrasts for each group of outcomes. If necessary, correspondent nonparametric tests will be used. The results will be described as 95% confidence intervals and considered significant at *P*<0.05.

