**Methods/Design:**

This is a protocol study for a parallel randomised controlled clinical trial. Eligible participants are older women (≥65 years) with a body mass index ≥30 kg/m ^2^ and hand grip strength ≤21 kg force. A total sample of 36 participants will be randomly allocated to one of the intervention groups in blocks of three: land-based, aquatic or control. Each intervention group will undergo 2-week sessions of a 10-week therapeutic exercise programme for strength, power and endurance training of the lower-limb muscles. Participants in the control group will not participate in any strengthening activity for lower limbs and will receive telephone calls once a week. Baseline and final evaluation of outcomes will encompass muscle performance of the lower limbs assessed by an isokinetic dynamometer; functional tests of usual walking speed, maximal walking speed (shuttle walking test), stair speed and the Short Physical Performance Battery; and health-related quality of life (Medical Outcomes Study Short Form Questionnaire – SF-36). Data collectors will be blinded to randomisation and will not be in touch with participants during the interventions.

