### Sample size

The effect size of the interventions was estimated at *f* = 0.20, based on previous studies of similar exercise programmes and the target population [15,26,27] and a pilot study conducted with 12 volunteers. The sample size was calculated assuming a mixed design of repeated-measures analysis of variance in the programme G* Power, version 3.1.2 [28], considering α = 0.05, β = 0.80, three groups and a correlation of 0.8 between the two repeated measures, with a resultant total of 30. Adding a possibility of 15% missing participants, the final sample size was calculated as 36, with 12 subjects per group. Figure 1 shows the flow diagram for participants in this study.

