### Randomisation

After complete baseline assessment, a randomisation sequence will be created using a computer-generated list of random numbers in block sizes of three. The allocation sequence will be concealed from the researchers enrolling and assessing participants, since it will be performed by an external researcher. The allocation of each participant will then be communicated to the researchers involved in the exercise programmes and to those responsible for monitoring the control group.

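### Intention-to-treat is promised, but the named two-visit repeated-measures ANOVA uses only women with both values; unless missing finals are imputed, the result is a complete-case analysis of about 30 or 31 of 36

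*Protocol article*

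**What the plan says.** The Statistical analysis section of the protocol article makes two commitments. On the population: "The effects of exercise programmes will be evaluated by intention-to treat analysis". On the model: "Repeated-measures analysis of variance for mixed design and two factors will be conducted with preplanned contrasts for each group of outcomes", with nonparametric counterparts if needed. On software: "we will use the Statistical Package for the Social Sciences version 15.0", with no procedure named.

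Two other sections determine what can be missing. The abstract gives two measurement occasions: "Baseline and final evaluation of outcomes will encompass muscle performance of the lower limbs assessed by an isokinetic dynamometer". The Randomisation section puts allocation after baseline: "After complete baseline assessment, a randomisation sequence will be created using a computer-generated list of random numbers in block sizes of three". Every randomised woman therefore has a baseline value.

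The only stated provision for missing women is in the Sample size section: "Adding a possibility of 15% missing participants, the final sample size was calculated as 36". The article gives no rule for a woman who has no final evaluation. It names no imputation, and it does not say that she is excluded.

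**The concern.** With two visits, the group-by-time test in a mixed-design ANOVA is the same as a one-way ANOVA on the change from baseline. A woman without a final value has no change, so she drops out of the comparison unless a value is supplied for her. A nonparametric counterpart based on change scores has the same requirement. The fixed model and the promised population agree only if a further step, which the article does not mention, is taken first.

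What is at stake is the randomised comparison and its label. The Discussion says that participants and those delivering the programmes cannot be blinded. The arms also ask very different things of the women: supervised sessions twice a week in the exercise arms, against weekly telephone calls and an instruction to avoid strengthening exercise in the control arm. Reasons for not returning could plausibly differ by arm. With 12 per arm, two women are 17% of an arm.

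**Working it through.** **1. The plan's own sample size.** Inputs from the Sample size section: f = 0.20, α = 0.05, three groups, two measurements, correlation 0.8, and 0.80 read as power. For the group-by-time interaction:

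- λ = f² × N × m / (1 − ρ) = 0.04 × N × 2 / 0.2 = 0.4N
- numerator df = (3 − 1)(2 − 1) = 2; denominator df = N − 3
- N = 27 gives power 0.794 and N = 28 gives 0.812. Rounding up to equal groups gives 30 (λ = 12, power 0.843).
- 30 / 0.85 = 35.3, rounded up to 36.

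The stated 30 and 36 are reproduced.

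**2. Complete pairs at the planned loss.** 36 × 0.85 = 30.6, so 30 or 31 women. Power is 0.843 at 30, 0.856 at 31 and 0.911 at 36. The planned loss does not take power below 0.80.

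**3. Effect scale for an illustration.** Assume that both exercise arms gain d, in units of the outcome SD, and that controls gain nothing. The variance of the three mean changes is 2d²/9. Matching the λ above requires this to equal 4f², so d = f√18 = 0.20 × 4.243 = 0.849 SD. The value depends on the assumed pattern: equally spaced arms would give f√24 = 0.98 SD for the best arm against control.

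**4. Three dropout patterns.** Simulated with 12 per arm, correlation 0.8 and a gain of 0.849 SD in both exercise arms (20,000 runs each). The change-score contrast is what the ANOVA estimates. The baseline-adjusted contrast is the maximum-likelihood estimate from a mixed model with a common baseline mean when all baselines are observed.

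| Pattern (assumed) | Target | ANOVA on complete pairs | Mixed model |
|---|---|---|---|
| The two women with the lowest baseline in each exercise arm lost | 0.85 | 0.79 | 0.85 |
| Two women per exercise arm lost who gain nothing | 0.71 | 0.85 | 0.85 |
| Six of 36 lost at random | 0.85 | 0.85 (SD of estimate 0.243) | 0.85 (SD 0.236) |

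In the first row loss depends on baseline and group: the ANOVA is biased downwards and the mixed model is not. In the second row loss depends on the unseen gain. The all-randomised value is 0.849 × 10/12 = 0.707, and both methods overstate it by the same ratio, 0.849 / 0.707 = 1.20. In the third row neither is biased and the mixed model is slightly more precise.

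**The case against.** The strongest reply is that nothing here is contradictory. Intention-to-treat says who is analysed and in which group; ANOVA is a model. Imputing missing finals would reconcile them, and a condensed article may leave that rule to a fuller document. This stands in part: the documents do not show that the trial will be analysed on completers only, and the absence of an imputation rule is not in itself a fault. What remains is that the article does fix a model, and that this model, taken as written, cannot use a woman without a final value.

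A reader might infer that the step from 30 to 36 confirms a planned exclusion of six women. It does not. Inflating for attrition is routine whatever missing-data method follows, and 30 or 31 is a planning allowance. Nor does stopping exercise mean leaving the analysis: a woman who stops attending sessions but returns for the final evaluation stays in the ANOVA.

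A reader might also infer that efficacy would be overstated by about 20%. That figure holds by construction, since two of 12 gaining exactly nothing gives 12/10 for any effect size. No passage says why women would leave, and loss of women with low baselines biases the other way.

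Finally, it may be objected that the mixed model does not repair the no-gain example. That is correct, as the second row of the table shows. The case for the model rests on the first and third rows, and the second needs a sensitivity analysis.

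**Conclusion.** The concern holds in a limited form. The article couples an intention-to-treat promise with a two-visit model that needs complete pairs. If missing finals are not imputed, 30 or 31 of 36 women would be analysed at the planned 15% loss, under a label that does not describe the analysis. There is no loss of power below the planned level. The size and direction of any bias are unknown: the illustrations run from 0.79 against a true 0.85 to 0.85 against a true 0.71, and each rests on an assumed dropout pattern, both exercise arms gaining equally, and the protocol's correlation of 0.8. The stronger reading, that the stated method cannot deliver intention-to-treat, is not supported. The change should be made, because a better-suited model is available in the software already named and costs little.

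**What to change.** - Make the primary analysis of each outcome a likelihood-based linear mixed model (SPSS MIXED) with visit, group-by-visit and one common baseline mean. Include all 36 randomised women in their allocated groups. This keeps the baselines of women who drop out, is valid if missingness depends on baseline or group, and is slightly more precise.
- State that the final evaluation already planned will be sought from every randomised woman, whatever her attendance.
- Add one sensitivity analysis in which missing final values in the exercise arms are imputed as control-like (no gain), because the mixed model does not correct outcome-dependent dropout.
- If the repeated-measures ANOVA is kept, label it complete-case and secondary, and report how many women per arm it uses.

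This takes a few sentences of analysis text and a few lines of syntax, with no extra participants or scheduled visits. The price is an explicit missing-at-random assumption in the primary model and a little more analysis work.

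### With one baseline and one final visit, the planned repeated-measures ANOVA is a valid change-score comparison; baseline-adjusted ANCOVA would be modestly more precise at very little cost

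*Protocol article*

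**What the plan says.** The Statistical analysis section fixes the model: "Repeated-measures analysis of variance for mixed design and two factors will be conducted with preplanned contrasts for each group of outcomes". It names no baseline covariate. The abstract shows two measurement occasions: "Baseline and final evaluation of outcomes will encompass muscle performance of the lower limbs assessed by an isokinetic dynamometer". The Sample size section uses the same model, "The sample size was calculated assuming a mixed design of repeated-measures analysis of variance in the programme G* Power", with "three groups and a correlation of 0.8 between the two repeated measures, with a resultant total of 30". The other inputs are "The effect size of the interventions was estimated at *f* = 0.20" and "considering α = 0.05, β = 0.80", where the second figure can only be the power. The allowance for losses follows: "Adding a possibility of 15% missing participants, the final sample size was calculated as 36, with 12 subjects per group".

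The Randomisation section says that the sequence is created after baseline assessment is complete, in blocks of three. It mentions no stratification on any outcome. The baseline value of each outcome is therefore a proper pre-randomisation covariate, and nothing else described in the article controls chance differences in it.

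**The concern.** With two occasions, the group-by-time interaction uses only each woman's difference between final and baseline value. This fixes the baseline coefficient at 1. When the correlation between visits is below 1 and the variances are equal, the best linear coefficient is the correlation itself. Forcing it to 1 over-corrects for baseline.

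Two things follow. Some precision is lost, which matters more in a trial of 36 women than in a large one. Also, in a sample where one arm happens to start lower, regression to the mean moves the change-score contrast in favour of that arm. With 12 women per arm such gaps are not rare, and the trial asks for a comparison of two active programmes as well as comparisons with control.

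**Working it through.** **Inputs.** From the Sample size section: f = 0.20, alpha = 0.05, power 0.80, k = 3 groups, m = 2 measures, rho = 0.8, N = 30 before and 36 after the 15% allowance. Assumed: equal variances at both visits (SD = 1), normal errors and a common slope.

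**1. Reproduce the plan's figure.** For the group-by-time test, lambda = f² × N × m / (1 - rho) = 0.04 × 2N / 0.2 = 0.4N, with 2 and N - 3 degrees of freedom.

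| N | Power |
|---|---|
| 27 | 0.794 |
| 28 | 0.812 |
| 30 | 0.843 |
| 36 | 0.911 |

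The smallest N with equal groups and at least 80% power is 30. Then 30 / 0.85 = 35.3, which rounds up to 36. The alternatives do not fit: at N = 30 the between-group main effect has power 0.15, and the time main effect already reaches 0.84 at N = 24. So the trial was sized on the interaction, that is, on the change-score comparison.

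**2. Residual variance.** Change score: 2(1 - rho) = 0.40. ANCOVA: 1 - rho² = 0.36. The ratio is (1 + rho)/2 = 0.90.

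**3. Small-sample cost.** Estimating the slope inflates the contrast variance on average by 1 + 1/(N - k - 2).
- N = 30: 0.90 × (1 + 1/25) = 0.936, a net reduction of about 6%.
- N = 36: 0.90 × (1 + 1/31) = 0.929, a net reduction of about 7%.

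Simulation at rho = 0.8 (40,000 runs) gave ratios of 0.94 and 0.93.

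**4. Power.** For ANCOVA, lambda = [0.16N / (1 - rho²)] / [1 + 1/(N - 5)], with 2 and N - 4 degrees of freedom. The 0.16 is the between-group variance of mean change implied by f = 0.20: 0.16N / 0.40 = 0.4N, as in step 1. The effect is held fixed as rho varies.

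| rho | N | Change score | ANCOVA |
|---|---|---|---|
| 0.8 (plan) | 30 | 0.843 | 0.865 |
| 0.8 (plan) | 36 | 0.911 | 0.930 |
| 0.6 (assumed) | 30 | 0.534 | 0.615 |
| 0.6 (assumed) | 36 | 0.626 | 0.714 |
| 0.5 (assumed) | 30 | 0.442 | 0.543 |
| 0.5 (assumed) | 36 | 0.525 | 0.640 |
| 0.9 (assumed) | 30 | 0.990 | 0.990 |

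At rho = 0.95 and N = 30 the net variance ratio is 1.014, a very slight loss.

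**5. Women saved at rho = 0.8.** ANCOVA gives 0.798 at N = 26, 0.817 at 27, 0.835 at 28 and 0.851 at 29. It first exceeds 80% at 27, against 28 for the change score. To match the planned 0.843 it needs between 28 and 29 women instead of 30. The saving is 1 to 2 women.

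**6. Bias and type I error.** Over repeated randomisation both estimates are unbiased: at N = 30 the simulated mean was 0.847 for each, against a true 0.849 SD (both exercise arms equal, control lower). The type I error was 0.049 to 0.051 for both. Conditional on an observed baseline gap D, the change-score contrast is off by -(1 - rho)D: 0.2 × 0.5 = 0.10 SD at rho = 0.8, and 0.5 × 0.5 = 0.25 SD if rho were 0.5.

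**7. How often such gaps occur.** With 12 per arm, the SD of a difference in baseline means is √(2/12) = 0.408. The chance of a gap above 0.5 SD in one given contrast is 2 × P(Z > 0.5/0.408) = 22%. The chance that some pair among the three arms differs by more than 0.5 SD is 44%.

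**The case against.** The strongest reply is that nothing here is wrong. The analysis named is the one the trial was sized on, the stated sample size reproduces under it, and it controls its error rate. At the only correlation in the document, "a correlation of 0.8 between the two repeated measures", the benefit is about 2 points of power. All of that stands.

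A reader might infer more than the document supports:

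- That the planned analysis is biased. It is not, over randomisation; only the estimate conditional on an observed baseline gap is shifted, and the gap may fall in either direction. At rho = 0.8 a 0.5 SD gap moves the contrast by 0.10 SD, about 12% of the 0.85 SD effect simulated.
- That ANCOVA is free. It spends one error degree of freedom and estimates a slope, which takes back over a third of the 10% large-sample gain at N = 30.
- That it saves three women (30 against 27). Most of that difference comes from rounding to equal groups.
- That the larger power gains are established. They need correlations of 0.5 to 0.6, which the document does not give, and above 0.8 the gain shrinks to nothing.

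On the other side, one correlation was assumed for the design, while the same model serves isokinetic strength and power, walking and stair speed, the Short Physical Performance Battery and the SF-36. The article gives no evidence that all of these reach 0.8, and ANCOVA gains most where they do not.

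**Conclusion.** The point holds as a cheap improvement to a valid plan. It is not an error, and no conclusion of the trial would be invalid without the change. At the plan's own correlation the gain is 6 to 7% in contrast variance and about 2 points of omnibus power. It would be about 8 to 12 points if an outcome correlated only 0.5 to 0.6, and practically nil from 0.9. The added benefit is removal of the conditional shift from chance baseline gaps.

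The algebra is certain. The size of the benefit rests on equal variances at the two visits, normal errors, a common slope, and the true correlation of each outcome, for which 0.8 is the only documented value.

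**What to change.** Make the primary analysis of each continuous outcome an ANCOVA of the final value on group, with that outcome's own baseline value as covariate. A mixed model with a common baseline mean across arms is equivalent. Report baseline-adjusted mean differences with 95% confidence intervals for the preplanned contrasts, and keep the repeated-measures ANOVA as a supportive analysis.

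The cost is one sentence in the analysis section, one error degree of freedom and the assumption of a common slope across arms. No new data are needed and the sample size can stay at 36. The Discussion places the analysis after the last randomised participant has finished, and the Trial status section describes recruitment as not yet complete, so on the article's account the change can still be specified before the results are analysed.

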## Discussion

To the best of our knowledge, this is the first randomised controlled trial designed to evaluate the benefit of resistance exercises for older people with sarcopenic obesity. Considering the obesity epidemic and sedentary habits of western populations in general, it is essential to find interventions that can address both problems. We chose to select only older women because of their greater longevity and higher risk of functional disabilities.

Providing assurance that rehabilitation techniques are really effective in an evidence-based way is important. To achieve this, we developed a study design using an appropriate power calculation to estimate the sample size. This clinical trial will provide substantial information about the effects of a common practice in the rehabilitation field. Exercise interventions are considered a nonpharmacologic and noninvasive technique that can improve functional capacity and prevent or reverse disabilities. If our hypothesis is correct, both intervention programmes will be effective, and the land-based intervention will produce better results for muscle performance and functional capacity. We will also investigate the effects on health-related quality of life.

Following the CONSORT Statement recommendations for randomised trials of nonpharmacologic treatments, we described our intervention protocols in detail, including all qualitative and quantitative components. Training and constant supervision will guarantee the programmes’ standardisation. In the interventions proposed in this protocol, it is not possible to blind participants or those administering the interventions. Researchers involved in outcomes assessment will thus be blinded to participant allocation and will have no contact with participants besides evaluation tests. Any harm or adverse events will be recorded and reported. Important to note is that it is completely feasible to carry out the exercise programmes proposed in this study in clinical settings. Our results will be analysed and published after discharge of the last randomised patient.

